### Phase 3: Evaluation

#### Quantitative analysis

Data collected from self-report questionnaires will be quantitatively analysed using the STATA software [32]. A detailed CONSORT diagram will be completed with fully annotated reasons for withdrawal from the study and follow-up rates where possible. This will also include numbers referred onto further specialist services during the study. Descriptive statistics of questionnaire data will be reported and inferential statistics, including mixed regression modelling, will investigate outcome variable associations. Growth curve analysis (linear and polynomial parameters), will be performed using MPlus [33] to calculate the fear of cancer recurrence trajectory and intercept link intervention and control groups. Interclass correlation coefficient (ICC) will also be determined to estimate the potential power required for future trials, based on the number of clusters and sample size per cluster. The Monte Carlo modelling approach within MPlus, advanced by Bolger and Laurenceau [34], will be utilised to determine the sample size required to estimate for a moderate effect of the difference in trajectory (i.e. slope coefficient) between intervention and control groups with covariates (age, treatment experience, disease severity). Alpha set to 0.05 (2-sided). Analysis will not be blinded and will be conducted by the local research teams (St Andrews and Stirling Universities) who will seek advice from a divisional statistician (St Andrews).

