**Methods:**

This study will run in four breast cancer centres in NHS Scotland, two intervention and two control centres. SBCNs at intervention centres will be trained to deliver the Mini-AFTERc intervention. Female patients who have completed primary breast cancer treatment in the previous 6 months will be screened for moderate FCR (FCR4 score: 10‑14). Participants at intervention centres will receive the Mini-AFTERc intervention within 2 weeks of recruitment. SBCNs will audio record the intervention telephone discussions with participants. Fidelity of intervention implementation will be assessed from audio recordings. All participants will complete three separate follow-up questionnaires assessing changes in FCR, anxiety, depression and quality of life over 3 months. Normalisation process theory (NPT) will form the framework for semi-structured interviews with 20% of patients and all SBCNs. Interviews will explore participants’ experience of the study, acceptability and usefulness of the intervention and factors influencing implementation within clinical practice. The ADePT process will be adopted to systematically problem solve and refine the trial design.

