### Trial design

This study is a non-randomised controlled pilot trial conducted within four breast cancer centres in NHS Scotland. The Mini-AFTERc intervention will be delivered at two of the sites in addition to standard care and compared to standard care alone delivered at the two control sites. The selection of cancer centres was dependant on the proximity of the research institutions and local knowledge of service provision. Guidance in relation to breast cancer follow-up after primary diagnosis is inconsistent [18]. Consequently, standard care (i.e. follow-up and support for patients once they have completed primary cancer treatment) can vary between cancer centres, in terms of timing and types of support offered. SBCNs at the intervention sites will be recruited and trained to deliver the Mini-AFTERc intervention using a pre-determined training programme, which will be further developed and refined with feedback from participating SBCNs during this trial.

Participants will be recruited from hospital clinics and over the telephone. Participants from intervention centres will receive an intervention telephone call within 2 weeks of recruitment. All participants (intervention and control) will be asked to report their FCR, mood and quality of life over a three-month follow-up period (Fig. 2). A bespoke smartphone application, already designed to collection questionnaire responses form patients, will also be tested as part of this pilot trial.

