#### Sample size

The trial aims to recruit 130 breast cancer patients, approximately 33 patients at each breast cancer centre. Researchers will screen patients until 65 patients have been recruited to the intervention group and 65 patients to the control group. Screening will continue until the target sample size has been reached. The anticipated recruitment period will take place over 12 months. An effect size of 0.5 at 0.85 power would require a sample of 130 patients to robustly demonstrate any effect of the intervention on patients’ fear of cancer recurrence, assuming a standard deviation of 7 between pre and post FCR measures, derived from a previous feasibility study [17], and an attrition rate of 30%.

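### An ICC from four centres, two per arm, is too imprecise for its stated use in estimating power for future trials

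*Protocol article*

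**What the plan says.** The Quantitative analysis section of the protocol article states: "Interclass correlation coefficient (ICC) will also be determined to estimate the potential power required for future trials", and adds that this is "based on the number of clusters and sample size per cluster". The next sentence describes a separate Monte Carlo step for sizing a comparison of trajectories between the groups. It lists age, treatment experience and disease severity as covariates and names no clustering term.

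The design behind that ICC is set out elsewhere in the article:

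- The Abstract gives "four breast cancer centres in NHS Scotland, two intervention and two control centres".
- Trial design makes centre and arm nested: "The Mini-AFTERc intervention will be delivered at two of the sites in addition to standard care and compared to standard care alone", with the other two sites as controls.
- The centres are a convenience choice: "The selection of cancer centres was dependant on the proximity of the research institutions and local knowledge of service provision".
- Trial design also expects real differences between centres, since standard care "can vary between cancer centres, in terms of timing and types of support offered".
- Sample size plans "approximately 33 patients at each breast cancer centre", with recruitment until "65 patients have been recruited to the intervention group and 65 patients to the control group", and assumes 30% attrition.

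The Discussion says the pilot is meant to supply the data needed to design a large-scale randomised trial. The article gives no anticipated ICC.

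**The concern.** The precision of an ICC depends mainly on the number of clusters, and far less on the number of patients in each. Four centres in two arms leave 4 - 2 = 2 degrees of freedom between centres after arm is accounted for. An ICC on that footing can be calculated, but it cannot distinguish negligible clustering from very heavy clustering.

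The article does not offer the ICC as a description of the pilot. It gives it a job: informing power for later trials. A low or zero estimate could persuade the planners that no allowance for clustering is needed, and a high one could make the later trial several times too large. Both could easily arise by chance from the same true value.

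**Working it through.** The article states no ICC, interval or design effect, so there is no figure of its own to reproduce. The only check of that kind is cluster size: 130 / 4 = 32.5, which agrees with the stated figure of about 33.

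**Inputs**

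- Centres k = 4 and arms = 2 (Abstract; Trial design). Between-centre df = 4 - 2 = 2.
- Patients per centre m = 32.5 with no loss, or 32.5 × 0.70 = 22.75 after 30% attrition (Sample size).
- Within-centre df = 4(m - 1) = 126 or 87.
- ICC values are assumptions; 0 to 0.10 is examined.
- Clusters are taken to be centres. The article does not define the term, but centres are the unit of allocation and the only unit given a size.

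**Step 1. Confidence interval for a given estimate r.** The F ratio that matches r is F = (1 + (m - 1)r) / (1 - r). Divide F by the 97.5% and 2.5% points of the F distribution on (2, 4(m - 1)) df, then convert each result x back with (x - 1) / (x + m - 1).

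For r = 0.05 and m = 22.75: F = (1 + 21.75 × 0.05) / 0.95 = 2.197. The F points on (2, 87) df are 3.850 and 0.0253.

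- Lower: 2.197 / 3.850 = 0.571, giving (0.571 - 1) / (0.571 + 21.75) = -0.019.
- Upper: 2.197 / 0.02533 = 86.8, giving 85.8 / 108.5 = 0.790.

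| Estimated ICC | 95% CI, m = 22.75 | 95% CI, m = 32.5 |
|---|---|---|
| 0 | -0.03 to 0.63 | -0.02 to 0.54 |
| 0.01 | -0.03 to 0.68 | -0.02 to 0.61 |
| 0.05 | -0.02 to 0.79 | -0.01 to 0.77 |
| 0.10 | 0.00 to 0.86 | 0.01 to 0.85 |

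Keeping every patient (m = 32.5) hardly narrows the interval. The limit is the number of centres.

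**Step 2. How the estimate behaves if the true ICC is known.** The ANOVA estimate is zero or below when the observed F ratio is at most 1. For a true ICC of 0.05 that means an F variate on (2, 4(m - 1)) df falling below 1/2.197 = 0.455 (m = 22.75) or 1/2.711 = 0.369 (m = 32.5).

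| True ICC (assumed) | P(estimate ≤ 0), m = 22.75 | P(estimate ≤ 0), m = 32.5 | Central 95% of estimates, m = 32.5 |
|---|---|---|---|
| 0.01 | 55% | 53% | -0.03 to 0.11 |
| 0.05 | 36% | 31% | -0.03 to 0.22 |
| 0.10 | 25% | 19% | -0.03 to 0.34 |

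**Step 3. What this means for a later trial, if it is cluster-randomised with 33 per cluster.** Design effect = 1 + (33 - 1) × ICC. With a true ICC of 0.05 it should be 1 + 32 × 0.05 = 2.6. Pilot estimates from zero or below up to 0.22 would imply anything from 1 to 1 + 32 × 0.222 = 8.1.

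For illustration, a standardised effect of 0.5 with 85% power and two-sided alpha of 0.05 needs 72 per arm, or 144 in total, before clustering and attrition. Multiplying by the design effect and rounding up gives 144 at ICC 0, 191 at 0.01 (144 × 1.32), 375 at 0.05 (144 × 2.6) and 605 at 0.10 (144 × 4.2). The intervals in Step 1 cannot separate these cases.

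**Step 4. If arm were left out of the model.** A real effect of 0.5 SD puts the four centre means at -0.25, -0.25, +0.25 and +0.25. Their variance is 4 × 0.0625 / 3 = 0.083, which by itself gives an apparent ICC of 0.083 / 1.083 = 0.077, or about 0.08. The treatment effect would then be counted as clustering.

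**The case against.** Several points on the other side are fair.

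- **A reader might infer that nesting centre in arm makes the ICC impossible to estimate.** It does not. A within-arm ICC exists once arm is a fixed effect; the difficulty is that it rests on 2 df.
- **A reader might infer that arm will be omitted, so that the ICC absorbs the treatment effect.** The article does not say so, and its planned models compare intervention with control. The figure of 0.08 is a warning about one way of fitting the model and does not describe the plan.
- **A reader might infer that this ICC alone will size the later trial.** The article describes a separate Monte Carlo step and does not say that a bare point estimate will be plugged in. Sizing is not among the three listed objectives either. However, the Monte Carlo description has no clustering term, so the pilot ICC is the only stated route by which clustering enters.
- **The design effects assume a cluster-randomised trial with about 33 per cluster.** The article says only that a large randomised trial will follow. With individual randomisation within centres this formula would not apply in the same form.
- **Negative values belong to the ANOVA estimator.** A mixed model would usually stop at zero, but the risk of a zero estimate remains.
- **Arm adjustment, intervals and sensitivity ranges are commonly left to a fuller document.** Their absence from the article is not the point here. The point is the stated use of the ICC, which no such detail can make adequate with four centres.

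**Conclusion.** The concern holds as a matter of precision. The article assigns the pilot ICC to power estimation for future trials, and 2 between-centre df cannot support that. An estimate of 0.05 would be compatible with anything from no clustering to an ICC near 0.8. If the true value were 0.05, about one pilot in three would show an ANOVA estimate of zero or below. The intervals follow from the design and the usual normal-theory one-way model with equal centre sizes. The chance of an estimate at or below zero also depends on an assumed true ICC, and the range of design effects (1 to about 8) further assumes a cluster-randomised successor with about 33 per cluster.

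Severity is minor to moderate. Nothing about this pilot's conduct or its participants changes; the cost would fall on the later trial, which will have its own protocol.

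**What to change.** In the Quantitative analysis section, state that the ICC of the follow-up outcome will be estimated with arm in the model and reported with its confidence interval for description only. State also that any clustering allowance in future power calculations, including the Monte Carlo step, will use a pre-stated range of externally sourced ICCs in place of the pilot point estimate. A range of 0.01 to 0.10 could serve as an example; it is an assumption to be confirmed against outside sources.

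An ICC of baseline FCR4 should not stand in for the follow-up ICC. Entry restricts that score to 10 to 14, so its variation between and within centres is curtailed by design.

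The cost is a sentence or two and a sensitivity table, with no change to recruitment or data collection. The downside is that the future sample size becomes a range instead of a single figure.

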#### Fidelity of intervention

A fidelity measure has been designed to assess the SBCNs’ adherence to the Mini-AFTERc intervention manual [35]. The fidelity measure will be applied to transcripts of the Mini-AFTERc intervention the audio recordings collected during the trial. The fidelity measure assesses adherence to key components (e.g. duration of discussion) of the intervention and scoring is informed by the principles of therapeutic alliance [36].

#### Qualitative analysis of interviews

The primary aim of the interviews is to assess the acceptability of the intervention to participants and the feasibility of incorporating the intervention into current NHS service provision. All interviews will be recorded on digital recorders and transcribed verbatim.

The interview schedule and analysis will be informed by normalisation process theory and its four main tenets: coherence, cognitive participation, collective action and reflexive monitoring [37]. It provides a constructive approach to explain and evaluate the underlying mechanisms of the implementation process and the components used to provide information for the optimisation of trial parameters [37]. The research team has experience of using NPT in the area of FCR among nurses [18]. However, further adaptation will be undertaken to align the component parts for the participant interviews.

#### Pilot trial evaluation

A process of decision-making after pilot and feasibility trials (ADePT) [38] will be used to evaluate the evidence from this pilot trial. The 3 key steps of ADePT facilitate the systematic appraisal of pilot and feasibility trials to identify all potential problems and solutions to these problems prior to the expansion of the trial. Findings from the quantitative data and analysis of interview data, from the perspective of patients and SBCNs, will support the decision-making process.

## Discussion

The Mini-AFTERc intervention has been designed to provide current cancer care professionals with a structured framework for discussing FCR with patients and assisting patients to address and reduce elevated levels of FCR at the end of primary cancer treatment. To our knowledge, Mini-AFTERc is the first brief FCR intervention, designed to assist individuals to manage moderate levels of FCR before they progress to more severe level and require a more intensive face-to-face psychological intervention. Preliminary feasibility work is promising, suggesting that Mini-AFTERc can feasibly be integrated into existing end-of-treatment cancer care practice, is acceptable to current cancer care staff and can effectively reduce FCR in patients affected by breast cancer [17, 18]. The proposed pilot trial will allow us to expand this feasibility work and determine the optimal approach to assess Mini-AFTERc in a controlled trial format.

SBCNs working in the UK recognise FCR as a primary concern of patient affected by cancer and many express a desire to receive training and develop the skills to better support patients with FCR [18]. The Mini-AFTERc intervention training programme has been specifically designed for SBCNs, to complement and develop the supportive skills that they already possess and have developed through routine practice. This pilot trial aims to further refine the Mini-AFTERc intervention training programme by allowing participating SBCNs to determine the focus of training sessions and provide feedback to the research team. Through this approach, we intend to develop a comprehensive but flexible training programme that can be appropriately and usefully delivered to SBCNs of different skill levels and across different centres.

Our feasibility work has determined that SBCNs may find the Mini-AFTERc intervention feasible and acceptable; however, we have yet to more broadly determine how patients may react to Mini-AFTERc. Involving patients at an early stage in research design is known to enhance the quality and appropriateness of research [39]. In keeping with our commitment to patient involvement in the development of this protocol, we intend to conduct comprehensive interviews with a representative sample of patients who participate in this trial. These interviews will explore patient thoughts about the Mini-AFTERc intervention, in terms of acceptability and usefulness, as well as their perceptions of participating in the trial. By considering and combining patient and nurse interviews with a structured decision-making framework (ADePT), we intend to refine the Mini-AFTERc intervention in addition to the trial structure and processes.

With this pilot work, we intend to collect the necessary data to design a large-scale randomised controlled trial of the Mini-AFTERc intervention. We believe this information will be beneficial for and of interest to patients affected by cancer as well as cancer services. We expect that this pilot trial will demonstrate that Mini-AFTERc is a feasible intervention that can be widely integrated into current cancer care practice and provide much needed emotional support to patients who have reached the end of cancer treatment.

## Data Availability

Not applicable.

## Abbreviations

ADePT: A process of Decision-making after Pilot and feasibility Trials
AFTER: Adjustment to the Fear, Threat or Expectation of Recurrence intervention
CARE: Consultation and Relational Empathy measure
CAREST-Trial: Cancer Recurrence Self-help Training Trial
CONSORT: Consolidated Standards of Reporting Trials
EQ-5D-5 L: EuroQol 5 Dimension Measure of Health-related Quality of Life
FCR: Fear of cancer recurrence
FCR4: Fear of cancer recurrence 4-item measure
HADS: Hospital anxiety and depression scale
ICC: Inter-class correlations
ICPV: Independent cancer patients’ voice
Mini-AFTERc: Adjustment to the Fear, Threat or Expectation of cancer Recurrence - brief (mini) intervention
MISS: Medical interview satisfaction scale
NCRI: National Cancer Research Institute
NHS: National Health Service
NPT: Normalisation process theory
RCT: Randomised controlled trial
SBCN: Specialist breast cancer nurses
SRM: Self-regulation model
SWORD: Survivors’ worries of recurrent disease
